## Potential Risks & Benefits

### Known Potential Risks

As this is a study of an intervention, the integrated HS+PlayReadVIP model, aimed to promote parent-chid relational health, parent mental health, and parenting behavior from birth to 24 months, compared with standard HS delivery. minimal risk to participants is expected.

Potential risks include:

1. Possible violation/loss of confidentiality
2. Anxiety or distress during assessment procedures due to discussion of sensitive personal information during surveys and in relation to their child’s developmental assessments
3. Concern about identification of child abuse or neglect, knowledge of an assault/exposure to domestic violence, criminality, or sensitive personal information.

Strategies to minimize risks:

1. *Violation/loss of confidentiality*: All physical paper records obtained from subjects, including questionnaires, video-recordings, and measures data, will be kept in locked file cabinets in locked rooms. In addition, all data will be de-identified prior to entering into data servers by removing subjects’ names and personal and demographic information and assigning them identification numbers. Electronic data will be stored in REDCap. Password protection, appropriate firewalls, and encryption systems will be in place to ensure privacy of information and the security and integrity of the electronically stored data. Cross-reference files (linking personally identifiable data with identification numbers) will only be made available to the PI and a limited number of research personnel if needed (e.g., for those staff responsible for merging information on sample members across data sources). For other team members conducting analyses, data will only be provided using the confidential ID numbers. All data will be reported in aggregate form, without identifying information or individual cases. Project staff will receive training on confidentiality, including data collection, data management, and reporting procedures, as well as on HIPAA-required procedures to ensure patient data confidentiality.
2. *Anxiety or distress due to discussion of sensitive topics*: Participants will be provided with contact information of the MPIs and their designees in case there is anything about the assessment or intervention procedures or their participation that is unclear, or that they do not understand, or they have questions or wish to report a research-related problem. Should the individual feel uncomfortable discussing his/her concerns with the project personnel, or about their rights as a research participant, contact information of the NYUGSOM IRB will be listed as advocates for their concerns.

Although unexpected, parents may feel some discomfort or anxiety due to questions that we ask or during child developmental assessments. However, all portions of the study are voluntary and families may elect to not answer questions or participate in measurements as they choose. In addition, families may withdraw from the study at any time without jeopardizing the care that they receive, and will be given answers to any questions that could arise throughout their participation in an effort to ease any discomfort or anxiety. Should parents experience an adverse reaction to the assessments and require medical and/or psychological assistance, project staff members will be trained to evaluate the situation and, if necessary, make appropriate referrals. Referrals will be made within the SPFHC medical home, and as needed to community based low-cost, high-quality service agencies on pre-existing processes for referral at the site.

1. *Concern about identification and reporting of child abuse/neglect, domestic violence, or other sensitive personal information*: We are required to disclose to the responsible authorities information we receive from subjects about child or other-family member maltreatment; and especially, intended physical harm and neglect to potential victims. Child maltreatment is defined as physical or mental injury, sexual abuse or exploitation, negligent treatment, or maltreatment of a child by a guardian, under circumstances that indicate that the child’s health or welfare is harmed or threatened. It is our legal and ethical responsibility to inform authorities and to protect the well-being of potential victims. Also, evidence of physical injury or neglect to a child (e.g., child abuse) or to an adult (e.g., domestic violence, elder abuse) caused by other-than-accidental means will be reported to the appropriate authorities. This procedure is explained to potential subjects both verbally and on the consent forms.

Additional Specific Considerations

1) Risks to pediatric participants: Minimal risk to child participants is expected. Assessment visits can result in boredom, performance anxiety, or fatigue. However, most children enjoy study assessment procedures which are designed to be experienced as play; participants may elect to withdraw at any time without penalty, and careful training will be provided to interviewers to recognize when children are refusing to participate in the assessments. Similarly, parents may become bored or distressed as a result of completing questionnaires and interviews about their child’s development. Examiners will be trained to provide appropriate support and follow-up, and personnel supervising assessments will be able to provide referrals should significant concerns about a child’s development arise. In addition, examiners will be trained to provide necessary logistical support to parents during assessments (e.g., if parents cannot read the questionnaires due to literacy levels). As with all studies, there are risks associated with breaches of confidentiality; however, our team will implement all Institutional Review Board (IRB) procedures approved for this study to minimize this risk.

2) Risk to care providers: HS+PlayReadVIP and other care providers may feel pressured to participate or to answer questions in a specific way. To mitigate this risk, passive recruitment methods involving a non-supervisory recruiter will be used and participants will be informed that all information provided will be kept confidential. In addition, interviewers will receive specific training to recognize when interviewees are feeling uncomfortable answering questions, and providers will be reminded that they can skip any questions they prefer not to answer. Finally, the study team will ensure that all participants understand that participation is voluntary and will not impact the status of their employment.

3) Alternative treatments and procedures: This is a preventive intervention. There are no alternative treatments and procedures. All families will receive standard pediatric care, including all screening and referral for all services as indicated in routine clinical practice. Families may receive the standard HealthySteps program, regardless of participation in the study, as they will have been screened as eligible.

### Risk of Use of Mobile Health Technology

NYULH MCIT-managed iPhones and iPads. These devices will be used in accord with the Terms of Service (TOS) and/or the End User License Agreements (EULA) provided by the product or device vendor. Use of such products and devices may result in loss of privacy and risk of breach of confidentiality. These products and devices will only be used to collect study data with IRB approval and if the subject has agreed to all applicable Terms of Service and EULAs. The participant will be advised to read the full EULA or TOS before agreeing to use the product. Any risks associated are outlined in the informed consent.

### Known Potential Benefits

The overall risk involved in the project is considered to be minimal, whereas the information gained could greatly improve our knowledge base about how to effectively integrate interventions in pediatric primary care to address heterogeneity in patient needs. Parents will complete standardized interviews and questionnaires about their own well-being, and their children’s development and behavior and their experience in the target intervention. Past research indicates that most parents appreciate having their attention drawn to the child's behavior and also being given an opportunity to talk about how they parent. Parents appear to enjoy the experience, which gives them a chance to discuss their own and their children's issues. Moreover, any positive (atypical) surveillance, screening, or evaluation results with clinical relevance will be discussed with the child’s parents and health provider, and the project will offer (and help facilitate) a referral for an Early Intervention evaluation up to age 3 years as needed. In addition, measures of maternal depression and parenting stress may lead to identification of parents in need of further evaluation and possible treatment; these parents will be offered referral for mental health services.

# Objectives and Purpose

The primary objective of this study is to evaluate the effectiveness and implementation of an integrated HealthySteps (HS) and Video Interaction Project (VIP) model (HS+VIP) in pediatric primary care to address disparities in Early Child Development (ECD).

## Primary Objective

There are two primary objectives of this study:

**Aim 1. Implement the optimized integrated HS+VIP model (formalized in Aim 1), and conduct an effectiveness-implementation study (Hybrid I design).**

1. Examine effectiveness of the integrated HS+VIP model, including parent mental health, parenting behavior, and early child development outcomes.
2. Examine implementation outcomes, including reach, appropriateness, acceptability, feasibility, and fidelity, using an integrated RE-AIM^18^ and CFIR^19^ framework.

**Aim 2. Examine health disparities mechanisms underlying effectiveness-implementation outcomes.** Using a mixed methods design, we will examine whether HS+VIP impacts are 1) mediated by impacts on parent assets/vulnerabilities and ERH or 2) moderated by CFIR contextual factors or RE-AIM domains.

# Study Design and Endpoints

## Description of Study Design

**Overall Study Design:**

Randomized Controlled Trial (RCT): 500 families will be enrolled between birth and 6 months of child age and randomized to 1) HealthySteps+PlayReadVIP or 2) standard HealthySteps; with intervention delivery and assessments of parenting assets/vulnerabilities, parenting practices/relationships and child development from enrollment to child age 2 years.

**1. Setting:** Enrollment, randomization, and intervention delivery will take place at the NYU Langone Sunset Park Family Health Centers (SPFHC) pediatric clinic. The SPFHC is a federally-qualified health center, consisting of co-located prenatal and pediatric clinics with 10 pediatric providers (nine pediatricians; one nurse practitioner) and designated space for intervention delivery and assessments. It is across the street from NYU Langone Hospital–Brooklyn (NYULHB). NYULHB has ~4,000 births/year with 25-30% pediatric follow-up at the SPFHC. In total from July 2021-June 2022, the SPFHC served 3,503 children ages 0-3 (84% Hispanic, 10% Black/African-American, 3% Asian). In a recent needs assessment, 54% of families surveyed (*n*=401) reported multiple needs related to ACEs and parenting.^137^ 96% of these families had insurance coverage through Medicaid or CHIP.

**2. Sampling:** A consecutive sample of 620 parent-infant dyads presenting to HCC pediatric clinic will be assessed for eligibility, with ~500 families enrolled (expected ~5% not meeting eligibility and refusal rate ~10-15%). Feasibility is based on the current rate of target-age dyads (~1000 newborns/year presenting for care at SPFHC), and will build upon processes developed for ongoing intervention studies at SPFHC and elsewhere. In addition, program and other care providers will be approached through passive recruitment methods to complete surveys and interviews related to program implementation.

**3. Eligibility criteria:** Parent/infant dyads enrolled between birth and 6 months. Specific inclusion/exclusion criteria are given in Section 4.

**4. Intervention:** HealthySteps+PlayReadVIP Additional details given in Section 6.

**5. Assessments and data collection:** For all participants, we will administer assessments at baseline, 12 months, and 2 years to measure outcomes (e.g., parenting assets/vulnerabilities, parenting practices/parent-child relationship, child development) and covariates (e.g., socio-demographics, biological risk). In addition, care providers will be asked to complete surveys and interviews at ther 12 month and 2 year assessment time points. All assessments will be completed by highly trained research assistants blind to group/intervention status. Additional details given in Section 7.

## Study Endpoints

### Primary Study Endpoints

Parent mental health, parenting practices, parent-child interaction, parent-child relationship, social determinants of health, child development, intervention feasibility, acceptability, reach, and participant engagement. These outcomes will be measured through surveys, interviews, parent-child observations, and direct assessments of child development (see Section 6 for additional details on specific measures).

### Secondary Study Endpoints

# Study Enrollment and Withdrawal

Study Enrollment and Withdrawal will include the following:

Enrollment:

- Participants will be parent-infant dyads and care providers recruited from the NYU Langone Sunset Park Family Health Center pediatric clinics.
- A total of 500 dyads and 25 care providers will be enrolled for the randomized controlled trial.
- Families will undergo baseline assessments, with follow-ups at multiple time points to evaluate parenting practices and relational health outcomes.

Withdrawal:

- Participants may withdraw at any time without penalty.
- Withdrawn participant’s data will be excluded from further analysis unless they have completed at least one follow-up.

In addition,

- Clinics or stakeholders may opt out at any stage.
- Data collected before withdrawal will be retained for aggregated implementation analysis.

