## Exclusion Criteria for parent-child dyads

An individual who meets any of the following criteria will be excluded from participation as a parent/child dyad in this study:

1. Non-singleton child
2. Parent is unable to provide consent
3. Parent does not speak English or Spanish, as study materials (e.g., questionnaires) are available in those languages
4. Parent has a severe medical or psychiatric impairment (e.g., intellectual disability, psychosis) that would interfere with study participation
5. Parent has plans to discontinue care at NYU Langone Health - Sunset Park Family Health Centers

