## Participant Withdrawal or Termination

### Reasons for Withdrawal or Termination

Participants are free to withdraw from participation in the study at any time upon request. An investigator may terminate participation in the study if:

- Any clinical adverse event (AE), laboratory abnormality, or other medical condition or situation occurs such that continued participation in the study would not be in the best interest of the participant
- The participant meets an exclusion criterion (either newly developed or not previously recognized) that precludes further study participation

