# Statistical Considerations

## Statistical and Analytical Plans

***Effectiveness Outcomes***

Initial ANOVA and Chi-square tests will be conducted to examine baseline equivalence of randomly assigned groups. Analyses with sex as a biological variable, including moderation and subgroup analyses, will be performed. Covariate entry (e.g., sociodemographics) will be decided based on model fit criteria, and sensitivity analyses will be performed for post-randomization risks.

Missing data and attrition: The research team has expertise in minimizing missing data. In addition, multiple imputation (MI)^160^ will be used to replace item-level data using the rich array of concurrently collected variables and prior responses. If an entire measure/survey is missing, we will use chained equations with lagged (in time) variables^161^ using all available information to build a large set of imputed datasets. Estimates will be combined using Rubin’s rules.^160^ When data are Missing at Random, likelihood-based methods provide unbiased estimates of population parameters even when panels are incomplete. In addition, we will use attrition analyses^162^ to examine whether attrition is related to baseline characteristics.

Tests of hypotheses: In order to examine the added value of HS+VIP in comparison to the standard HS model, we will focus on outcomes related to ERH and ECD where we expect the effects of standard HS to be substantially smaller than the integrated HS+VIP model. Impact analyses at each assessment timepoint will be conducted using ordinary least squares (OLS) regression in an intent-to-treat (ITT) framework, adjusted for baseline sociodemographic covariates. In addition, structural equation models (SEM)^163^ will be used to examine family outcomes over time. This will allow us to examine whether initial levels and trajectories in parent well-being, parent-child interaction, and ECD vary between participants, and whether that variation is explained by assignment to HS+VIP or standard HS.

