### Adherence and Retention Analyses

Participant engagemet in the intervention (e.g., number of possible sessions attended) and fidelity of intervention delivery (e.g., number of program components delivered at each session) will be tracked from the medical record and presented using summary statistics. As noted above, missing data and attrition analyses will be conducted to determine if data is missing at random or missing completely at random, and multiple imputation will be used to account for missing data.

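### The withdrawal rule in Section 5 drops randomised families who leave before a first follow-up, contradicting the intent-to-treat, imputation and attrition analyses promised in Section 9

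*Protocol*

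**What the plan says.** Section 5 (Study Enrollment and Withdrawal) sets the handling rule: a withdrawn participant's "data will be excluded from further analysis unless they have completed at least one follow-up". The only sentence there that keeps earlier data is limited in scope: "Data collected before withdrawal will be retained for aggregated implementation analysis". That does not cover effectiveness.

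Section 9.1 (Effectiveness Outcomes) goes the other way: "Impact analyses at each assessment timepoint will be conducted using ordinary least squares (OLS) regression in an intent-to-treat (ITT) framework". For a wholly missing instrument it says: "If an entire measure/survey is missing, we will use chained equations with lagged (in time) variables". The same section plans to test whether dropout is associated with baseline characteristics. Section 9.4.2 (Adherence and Retention Analyses) repeats that "multiple imputation will be used to account for missing data".

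Section 5.7.1 (Reasons for Withdrawal or Termination) lets an investigator end a family's participation, for example when "The participant meets an exclusion criterion (either newly developed or not previously recognized) that precludes further study participation". It does not say what then happens to that family in the analysis.

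**The concern.** Intent-to-treat means that a family's place in the comparison is fixed at randomisation. The Section 5 rule makes it depend on something that happens later. Baseline is collected before randomisation (Section 9.6.1), the first follow-up is at Day 180 +/- 90 (Section 7.3), and participants are not masked (Section 9.6.1). Families therefore know their arm for roughly three to nine months before the rule stops applying to them. Leaving in that window can depend on arm and on prognosis.

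The rule is also uneven. It names withdrawn participants only. A family that stops answering calls has its outcomes imputed, while a family that says it is leaving is deleted, although both have a baseline and nothing after it.

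Read literally, the rule also takes leavers' baseline data out of the attrition analysis, which cannot be done without them. If the conflict stays in the protocol, someone must choose between Sections 5 and 9 when withdrawals by arm may already be known.

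**Working it through.** **1. Sections side by side, for a family randomised and withdrawn before the 12-month assessment.**

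| Provision | Treatment of this family |
|---|---|
| Section 5 | Excluded from further analysis |
| Section 9.1, impact analyses | In the comparison, in its assigned arm |
| Section 9.1 and 9.4.2, missing data | Missing measures imputed |
| Section 9.1, attrition analysis | Baseline data needed |

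The first row is incompatible with the other three.

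**2. Search for a reconciling provision.**
- Section 9.3 (Analysis Datasets) describes files and storage. It defines no modified intent-to-treat set.
- Section 9.6.1 says that participants who discontinue are not replaced, so the gap is not filled.
- The Participant and Data Confidentiality section lets the investigator keep using information collected before an authorisation is revoked, so privacy rules do not force the exclusion.

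**3. The plan's own figure.** Section 9.5 claims more than 80% power for d = .3 with 400 families at alpha = .05. Assume 200 per arm and a two-sided test: power = Phi(0.3 x sqrt(200/2) - 1.96) = Phi(3.00 - 1.96) = Phi(1.04) = 0.85. The claim reproduces. Because 500 x (1 - 0.20) = 400 already allows for attrition, the rule does not alter stated power. The issue is bias and consistency.

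**4. How many families.** Attrition of 15-20% by 24 months is 500 x 0.15 = 75 to 500 x 0.20 = 100 families. This covers all causes and both follow-up intervals. Section 9.5 does not separate early from late exit, or withdrawal from loss to contact. The number caught by the rule is therefore at most 75-100 under the plan's attrition assumption, and otherwise unknown.

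**5. What the bias could look like (illustration only).** Let p be the share of an arm excluded and s the amount by which excluded families score below retained ones, taken as equal in both arms. The retained mean exceeds the full mean by p x s, so the unadjusted contrast shifts by (p1 - p2) x s. None of these values is in the protocol:

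| Difference in exit | s = 0.3 SD | s = 0.5 SD | s = 0.8 SD |
|---|---|---|---|
| 0 points | 0 | 0 | 0 |
| 4 points | 0.012 | 0.020 | 0.032 |
| 10 points | 0.030 | 0.050 | 0.080 |

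The non-zero entries run from 0.012/0.30 = 4% to 0.080/0.30 = 27% of the planned effect.

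**6. What imputation would recover.** The table concerns an unadjusted comparison of observed families. The plan adjusts for baseline sociodemographic covariates. If only the outcome is missing and it is imputed from the covariates already in the regression, imputation reproduces the regression fitted to observed families, and the two estimates agree. A simulation of 500 families illustrates this (true effect .30, exit about 16-20% versus 6-8%, leaver deficit 0.45-0.49 SD, covariate R-squared .25, all assumed). Adjusted deletion and imputation both gave .303 when exit followed the covariate, .353 when it followed unmeasured factors, and .339 when it followed the outcome.

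A gain therefore requires baseline variables outside the regression. The assessment table in Section 7.1.1 offers four constructs: depression, stress, self-efficacy and social support. The relationship, StimQ and child measures have no baseline score, so little can be recovered for them.

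**The case against.** The strongest reply is that restoring these families may barely move the estimate, for the reason in step 6. That stands. It removes any claim that the fix recovers a stated fraction of d = .30. It does not remove the contradiction, or the need to settle analysis membership before outcomes are seen.

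A milder reading is also possible: exclusion from further analysis might mean outcome analysis only, leaving baseline data for the attrition test. That would resolve one of the conflicts. The conflict with intent-to-treat and imputation would remain.

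Three stronger inferences are tempting, and the protocol does not support them.
- A reader might infer that the Section 5.7.1 grounds, combined with exclusion criteria such as "Parent has plans to discontinue care at NYU Langone Health - Sunset Park Family Health Centers", already delete families for outcome-related reasons. Section 5.7.1 concerns participation, is discretionary, and separates termination from withdrawal. Whether Section 5 reaches terminated families is simply not stated.
- A reader might infer that the arms differ in session burden and so will lose families at different rates. The protocol states no such difference. Both arms are seen at well-child visits, and Section 6.1 presents the combined model as time-saving.
- A reader might conclude that families who newly meet an exclusion criterion should stay in the 12- and 24-month assessments. That would be a new participation rule, and it fits badly with criteria such as inability to consent.

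**Conclusion.** The Section 5 sentence is wrong as written. It conflicts with the intent-to-treat framework, the imputation of wholly missing measures and the attrition analysis, and no other provision requires or reconciles it. Because it acts after randomisation with participants unmasked, it opens a route to an exclusion that differs by arm. The wording is the same for both arms, and the protocol gives no evidence that an imbalance will occur.

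The size cannot be derived. Under the plan's attrition assumption, 75-100 of 500 families is an upper bound on those affected. A reader might take the 4-27% of d = .30 in the illustration as the expected distortion. It is not: it rests on assumed exit differences and leaver deficits, ignores covariate adjustment, and is not what imputation would give back. The conclusion rests on the conflict between the sections, not on those percentages.

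**What to change.** Replace the Section 5 sentence with wording such as: *All randomised dyads are included in the ITT analysis in their assigned arm. Data collected before withdrawal are retained, as the confidentiality section allows. Missing outcomes are handled as in Section 9.1 whatever the reason, with the baseline depression, stress, self-efficacy and social support scores in the imputation model. An analysis excluding dyads without follow-up is at most a sensitivity analysis.*

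Add that the same analysis membership applies to families whose participation is terminated under Section 5.7.1, and leave the rules for continued participation as they are.

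The cost is a short text amendment. The imputation is already planned and the four sets of baseline scores are already collected, so no extra visits, families or measures are needed.

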## Participant and Data Confidentiality

Information about study subjects will be kept confidential and managed according to the requirements of the Health Insurance Portability and Accountability Act of 1996 (HIPAA). Those regulations require a signed subject authorization informing the subject of the following:

- What protected health information (PHI) will be collected from subjects in this study
- Who will have access to that information and why
- Who will use or disclose that information
- The rights of a research subject to revoke their authorization for use of their PHI.

In the event that a subject revokes authorization to collect or use PHI, the investigator, by regulation, retains the ability to use all information collected prior to the revocation of subject authorization. For subjects that have revoked authorization to collect or use PHI, attempts should be made to obtain permission to collect at least vital status (i.e. that the subject is alive) at the end of their scheduled study period.

Participant confidentiality is strictly held in trust by the participating investigators, their staff, and the sponsor(s) and their agents. This confidentiality is extended to cover testing of clinical information relating to participants. Therefore, the study protocol, documentation, data, and all other information generated will be held in strict confidence. No information concerning the study or the data will be released to any unauthorized third party without prior written approval of the sponsor.

The study monitor, other authorized representatives of the sponsor, or representatives of the IRB may inspect all documents and records required to be maintained by the investigator, including but not limited to, medical records (office, clinic, or hospital) and pharmacy records for the participants in this study. The clinical study site will permit access to such records.

The study participant’s contact information will be securely stored at each clinical site for internal use during the study. At the end of the study, all records will continue to be kept in a secure location for as long a period as dictated by local IRB and Institutional regulations.

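### Excluding dyads that withdraw before completing a follow-up contradicts the protocol's own intent-to-treat, imputation and attrition plans

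*Protocol*

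**What the plan says.** Under Study Enrollment and Withdrawal, the protocol states that a withdrawn participant's "data will be excluded from further analysis unless they have completed at least one follow-up". A later bullet in that section adds: "Data collected before withdrawal will be retained for aggregated implementation analysis". That bullet follows one about clinics and stakeholders opting out, so it is unclear whether it covers families.

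Under Statistical and Analytical Plans, Effectiveness Outcomes, impact at each timepoint is estimated by "ordinary least squares (OLS) regression in an intent-to-treat (ITT) framework, adjusted for baseline sociodemographic covariates". On missing data: "If an entire measure/survey is missing, we will use chained equations with lagged (in time) variables", drawing on all available information. Attrition analyses are planned "to examine whether attrition is related to baseline characteristics". Adherence and Retention Analyses repeats that "multiple imputation will be used to account for missing data". None of these statements makes an exception for early withdrawals.

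Two other statements bear on the point. Baseline assessments are completed before randomization (Study Specific Procedures; Enrollment Procedures). Under Participant and Data Confidentiality, an investigator whose subject revokes authorization "retains the ability to use all information collected prior to the revocation of subject authorization".

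**The concern.** The withdrawal rule and the analysis section give different instructions for the same family. Follow-ups are scheduled at 12 and 24 months only, so the rule removes any dyad that withdraws with neither completed, chiefly those leaving before 12 months. The baseline data of these families are what the imputation and the attrition analysis would use.

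The rule also treats the same missing data in two ways. A family that stops responding stays in the intent-to-treat set and has its outcomes imputed. A family that says it is withdrawing is dropped.

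Withdrawal happens after an assignment that families and interventionists know, and only one arm adds video-recorded sessions, so the reasons for leaving could differ by arm. If they do, the effectiveness comparison is no longer between the groups as randomized, and an attrition analysis without the earliest leavers would not show it. With two conflicting rules in force, the choice of analysis set could also be made after the data are seen.

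**Working it through.** **1. Side-by-side check.** Take a dyad that completes baseline, is randomized, and formally withdraws before 12 months.

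| Protocol statement | What happens to the dyad |
|---|---|
| Withdrawal rule | Excluded from further analysis |
| Intent-to-treat impact analysis | Kept in its assigned arm |
| Chained-equation imputation | 12- and 24-month measures imputed |
| Attrition analysis on baseline characteristics | Counted as lost, baseline data used |
| Confidentiality section | Use of data already collected is allowed |

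The first row cannot be followed together with the next three. The last row shows that nothing in the protocol compels the exclusion.

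**2. The plan's own figures.** Sample Size gives 500 enrolled, attrition of 15-20% by 24 months, a final 400, d = .30 and alpha = .05.
- 500 × .15 to 500 × .20 = 75 to 100 families lost; 500 × (1 − .20) = 400.
- With 200 per arm, d = .30 and two-sided alpha .05 (sidedness is assumed), power is 85.1% by the normal approximation and 84.9% by noncentral t.

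This agrees with the stated power of more than 80%. The withdrawal rule changes neither figure. The protocol does not say how much of the 15-20% is formal withdrawal before 12 months, or how it splits by arm.

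**3. Simple formula for the bias.** Let w be the share of an arm excluded and g the gap in SD between retained and excluded families in that arm. Then bias = wT·gT − wC·gC, where T is HS+PlayReadVIP and C is standard HS. All values of w and g below are assumed.
- Equal shares and equal gaps: 0.
- 10% v 5%, g = .2 to .5: .05 × .2 = .010 to .05 × .5 = .025 SD (3-8% of .30).
- 15% v 5%, g = .2 to .5: .10 × .2 = .020 to .10 × .5 = .050 SD (7-17% of .30).
- 10% in both arms, gaps .5 and 0: .10 × .5 = .05 SD (17% of .30).

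This formula makes no allowance for covariate adjustment.

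**4. Simulation of the effect of adjustment.** Assumptions: 250 per arm, no true effect, baseline score correlated .5 with the outcome, 5% random withdrawal in control, and 5%, 10% or 15% withdrawal in the other arm concentrated in families with worse baseline scores. Withdrawn families are excluded.

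| Analysis after exclusion | Bias in SD at 5 / 10 / 15% |
|---|---|
| Unadjusted difference | about .03 / .05 / .08 |
| OLS adjusted for the score that drives withdrawal | about 0 / 0 / 0 |
| OLS adjusted for a covariate correlated .3 with that score | about .03 / .05 / .07 |

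Type I error in the unadjusted row is about .06 / .09 / .13 against a nominal .05. In the last row, .03/.30 = 10%, .05/.30 = 17% and .07/.30 = 23% of the planned effect.

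**5. Which row is closest to the plan?** The protocol adjusts for sociodemographic covariates and decides covariate entry by model fit. In its measures table, depression, stress, self-efficacy and social support are collected at baseline. The relationship scale, StimQ, social competence and language measures are not. So the second row is not assured, and the third is a reasonable illustration.

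**The case against.** The strongest objection is about size. When withdrawal depends only on arm and a measured baseline variable, OLS on the remaining families adjusted for that variable is unbiased, as is imputation from it. The larger figures above (.08 SD, type I error about .13) come from an unadjusted comparison, which is not the planned one. This stands, and those figures should not be quoted as the expected harm. It does not remove the problem, because the plan names sociodemographics only.

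A second objection also stands in part. The focal outcomes mostly have no baseline measurement, so a baseline correlation of .5 is unsupported for them. With weaker predictors both the simulated bias and the benefit of imputation shrink.

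Four stronger readings are tempting but not supported:
- *Families vanish from every analysis.* The retention bullet may keep their data for aggregated implementation analysis. Its scope is unclear, and it does not return them to the effectiveness comparison.
- *The trial is fully open.* Families and interventionists are unmasked, but those collecting data are masked. The route to bias is arm-dependent withdrawal.
- *The withdrawal-handling heading, listed in the contents without body text, proves there is no other rule.* Several other listed headings also lack text, so this carries little weight.
- *The matter can be left to the SAP.* A SAP can add detail, but the protocol already states both rules, and following either breaks the other.

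**Conclusion.** The withdrawal sentence is wrong as written. It contradicts the protocol's intent-to-treat, imputation and attrition statements, and it conditions the effectiveness comparison on an event after randomization. That conclusion rests on the text and needs no assumed rates.

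A reader might infer that the result will be biased by a known amount. The documents do not support this, because they give no early-withdrawal rate by arm. Bias is zero if the share withdrawing and the outcome gap are the same in both arms, or if the model adjusts for what drives withdrawal. It is about .03 to .07 SD under the assumed 5-15% baseline-dependent withdrawal in one arm with weakly related covariates. The rule covers formal withdrawal, not loss to follow-up. The final sample of 400 and power of about 85% stand.

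**What to change.** Delete the exclusion sentence under Study Enrollment and Withdrawal and state instead that:
- every randomized dyad stays in the intent-to-treat set in its assigned arm;
- data collected before withdrawal are used, as the confidentiality section allows;
- missing outcomes are handled by the planned chained-equation imputation, with arm and the collected baseline measures (depression, stress, self-efficacy, social support, sociodemographics) in the model;
- withdrawals before 12 months enter the attrition analysis and are reported by arm.

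Add a missing-not-at-random sensitivity analysis. Imputation from baseline alone is unbiased only under missing at random, so keeping these families does not by itself guarantee an unbiased result.

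The cost is a protocol wording change and a little more analysis work. No extra data or families are needed.
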